## Abstract

**Introduction:**

About 44% of Aboriginal and/or Torres Strait Islander women smoke during pregnancy compared to 12% of their general population counterparts. Evidence-based quit smoking advice received from health care professionals (HCPs) can increase smoking cessation rates. However, HCPs lack culturally appropriate smoking cessation training, which is a major barrier to provision of smoking cessation care for this population.

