### Intervention

Participating sites and their HCPs will have the option to choose one of the two iSISTAQUIT training packages available (Table 1).

**Table 1 pone.0274139.t001:** iSISTAQUIT package options.

Characteristics	Option 1: Evaluation-Research package (includes CPD points)	Option 2a: Training package with CPD points	Option 2b: Training Package without CPD points
iSISTAQUIT training	Yes	Yes	Yes
Research component	Yes	No	No
Surveys to complete	All surveys	Only pre- and immediate post-training HCP surveys acknowledged by HPMI as being done or not (irrespective of content) for CPD points	No surveys
Data collection	Medical practice software via Pen CS iSQ Topbar app (ABCD template) or Communicare iSQ clinical item (ABCD template)	None	None
Resources	Online training modules + treatment manual + patient flipchart + My journey booklet + NRT posters + ABCD desk mousepad + medical practice software templates + CO monitor/s + oral NRT	Online training modules + treatment manual + patient flipchart + My journey booklet	Online training modules + treatment manual + patient flipchart + My journey booklet
Option to get CPD points	Yes	Yes	No

ABCD: A-Ask/Assess, B- Brief Advice, C-Cessation, D- Discuss psychosocial context (of smoking)

CPD: Continued professional development

HPMI: Hunter Postgraduate Medical Institute

iSQ: iSISTAQUIT

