#### Option 1. Evaluation research package

HCPs will be required to consent to completing the self-paced training modules, the reflective workbook and the pre- and post-training surveys (4 surveys in total). The training surveys will provide evidence on changes in knowledge, attitude and behaviours of the HCPs related to smoking cessation care. HCPs will be entered into a prize draw for completing all surveys and will have an option to claim CPD points.

The full iSISTAQUIT Evaluation-Research package consists, in addition to the training resources (treatment manual, patient flipchart and My Journey (patient) booklet), a) the provision of a carbon monoxide meter and oral nicotine replacement therapy (NRT), and, b) the choice of two medical practice software templates (Pen CS Topbar or Communicare) which aid and support the HCPs to enter the data about the patient’s medical consultation and the characteristics of the women’s quit attempts. The templates will be also utilised to guide the consultation according to the training using the ABCD approach [43]. ABCD approach stands for A—ask/assess; B—brief advice; C—cessation; and D—discuss the psychosocial context of smoking. This approach has been previously used in ICAN QUIT in Pregnancy and the SISTAQUIT RCT project.

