	3. Secondary outcomes	1. Smoking cessation rate: Percentage of women who change their smoking status (PTA, CCI) 2. Pregnant women participation rate: • Number of pregnant women who receive any iSISTAQUIT ABCD component/ number of eligible women seen by the service (PTA, CCI) • Number of pregnant women who receive My Journey booklet/ number of eligible women seen by the service (PTA,CL)	• PenCS Topbar application or web-based version for iSISTAQUIT (ABCD template) • Communicare iSISTAQUIT Clinical item (ABCD template) • Communicare iSISTAQUIT (smoking status) The ABCD tool includes a question that explores if the pregnant women quit smoking for at least 24 hours during the last 2 weeks, this question if available in the electronic medical records (PenCS Topbar application or web-based version for iSISTAQUIT or the Communicare iSISTAQUIT Clinical item). Additionally, a specific question regarding to the smoking status ‘do you smoke’ will be asked and recorded in Communicare. For all pregnant women that reported that they smoke, the status will be followed up and a percentage of the women that change of status reported by service.
Adoption	1. Practitioner participation rate	• Number of HCP who completed the training/ Number of HCPs who commenced the training (OM) (three separate rates calculated for HCPs who applied for CPD points, did not apply for CPD points and combined irrespective of CPD points). Rates will be compared statistically to determine if it’s worthwhile offering CPD points to improve uptake of training.	• Online (through Moodle, HPMI)
	2. Component adoption rate	• Four separate rates will be calculated for consultations in which A, B, C or D sections of the ABCD template were completed. This will be calculated by dividing number of respective completions (A, B, C or D) divided by number of consultations prompted by the app. The average component rate will be estimated for each component as the sum of the rates from each service divided by the number of participating services (PTA, CCI)	• PenCS Topbar application or web-based version for iSISTAQUIT (ABCD template) • Communicare iSISTAQUIT Clinical item (ABCD template)

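### The B, C and D adoption rates share A's denominator, so if the app also prompts for women who do not smoke they mix smoking prevalence with delivery of care

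*Protocol article*

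**What the plan says.** The component adoption rate is the second Adoption outcome in Table 2 of the protocol article. "Four separate rates will be calculated for consultations in which A, B, C or D sections of the ABCD template were completed", and each is obtained by "dividing number of respective completions (A, B, C or D) divided by number of consultations prompted by the app". The four rates therefore have one common denominator. The overall figure for each component is "the sum of the rates from each service divided by the number of participating services", an unweighted mean of the service rates.

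The section on Option 1 (Evaluation research package) spells out the letters: "ABCD approach stands for A—ask/assess; B—brief advice; C—cessation; and D—discuss the psychosocial context of smoking". The footnote to Table 1 gives the same meanings.

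The article does not say what makes the app prompt. It could be any pregnancy, a pregnancy in an Aboriginal or Torres Strait Islander woman, or a recorded smoker. Nor does it say whether B, C and D are left blank once A shows that the woman does not smoke.

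**The concern.** A can be completed for any woman. B, C and D, read by their names, have content mainly for a woman who smokes or is trying to quit. If prompts reach non-smokers, a consultation in which A is completed and the rest does not apply adds to the denominator of all four rates but to the numerator of A only. It then looks the same as a consultation with a smoker in which advice and cessation support were left out.

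Two readings of the results are at stake. A low C or D rate could be taken as practitioners omitting cessation care, when part of it only reflects how many prompted women smoke. And one of the protocol's stated objectives is to compare Aboriginal and Torres Strait Islander services with Mainstream services. If these rates were used for that, or simply compared between sites, a difference in smoker share would appear as a difference in adoption.

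**Working it through.** The article gives no value or target for these rates, so there is no figure to reproduce. The check is an identity.

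**Inputs**
- s: share of prompted consultations in which the woman smokes. The article does not give it. If all pregnant Aboriginal and/or Torres Strait Islander women are prompted, the article's own prevalence applies: s = 44% (Abstract and Introduction). Values of 60% and 80% are assumptions for partly selective prompting. s = 100% means that only smokers are prompted.
- c: share of consultations with smokers in which the component is completed. Not given; 50%, 70%, 80% and 100% are assumed.
- d: share of consultations with non-smokers in which the component is completed. Not given.

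**Formula**

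Reported rate = s × c + (1 − s) × d.

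If B, C and D are completed only for smokers, d = 0 and the reported rate is s × c, with a maximum of s. If s = 100%, the rate is c and the denominator does no harm.

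**Reported rate for B, C or D with d = 0**

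| s | c = 50% | c = 70% | c = 80% | c = 100% (ceiling) |
|---|---|---|---|---|
| 44% | 22.0% | 30.8% | 35.2% | 44% |
| 60% | 30.0% | 42.0% | 48.0% | 60% |
| 80% | 40.0% | 56.0% | 64.0% | 80% |
| 100% | 50.0% | 70.0% | 80.0% | 100% |

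**Comparison of services** (s = 80% is assumed)
- Same practice, different rates: with c = 70% at both, a service with s = 44% reports 0.44 × 0.70 = 30.8%, and one with s = 80% reports 0.80 × 0.70 = 56.0%.
- Different practice, same rate: s = 44% with c = 100% gives 44%; s = 80% with c = 55% gives 0.80 × 0.55 = 44%.
- Unweighted mean: for the two services with c = 70%, (30.8% + 56.0%) / 2 = 43.4%, although both deliver the component to 70% of smokers.

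**With smokers as the denominator** the rate is (s × c) / s = c, whatever s is: 70% at both services, and 70% on average.

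**The case against.** The strongest objection is that the article states neither condition behind the cap. The prompt trigger is undefined, and the idea that B, C and D are skipped after a negative A is inferred from the section names. Some text fits a template used with smokers only: it lets practitioners "enter the data about the patient’s medical consultation and the characteristics of the women’s quit attempts", and it includes an item on recent quitting. Trigger and completion rules are also the kind of software detail that an article may leave to the full protocol.

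This stands as far as it makes the cap conditional. It does not remove the point, because the article does print the formula, and the formula has no restriction to smokers. Other text leans towards non-smokers being included. The first section asks and assesses, and Table 2 says that "a specific question regarding to the smoking status ‘do you smoke’ will be asked and recorded in Communicare" and then follows the status of those who report smoking, a subset of the women asked.

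Two stronger readings are tempting and are not supported:
- A reader might take the general-population prevalence of 12% in "About 44% of Aboriginal and/or Torres Strait Islander women smoke during pregnancy compared to 12% of their general population counterparts" as the ceiling at Mainstream sites. Nothing says that the template is prompted for the general population, and Mainstream sites are sought because they see many pregnant Aboriginal and Torres Strait Islander women.
- A reader might infer that the study cannot show whether smokers received the care. Smoking status is recorded, and it could supply the right denominator if the extract keeps the link to B, C and D.

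It is also fair that completion per prompt is a legitimate measure of template use. That is a reason to keep the present rate alongside the new one. Finally, the article specifies no comparison of these particular rates between service types, so the effect on that objective arises only if they are used in that way.

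**Conclusion.** The point holds in conditional form. The shared, unrestricted denominator is on the page. If the app prompts for non-smokers and B, C and D are completed only for smokers, these three rates measure smoker share times delivery. The ceiling is then about 44% if every pregnant Aboriginal and/or Torres Strait Islander woman is prompted, and 70% delivery (an assumed value) would be reported as 31%. Rates from services with different smoker shares would not be comparable, and their unweighted mean would inherit the mixture. If only smokers are prompted, there is no bias. If the sections are sometimes completed for non-smokers, the distortion lies in between.

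This concerns a descriptive process outcome with no target or threshold attached. It does not touch the powered comparison of practitioner survey scores. It is still worth settling in advance, because Table 2 (Maintenance) describes the template data as de-identified quarterly aggregates. A split by smoking status that is not built into them may not be recoverable later.

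**What to change.** State in Table 2 what triggers a prompt. Keep prompted consultations as the denominator for A. For B, C and D, keep the present rate as a measure of template use if wanted, and also report completions divided by prompted consultations in which the woman is recorded as smoking or in a current quit attempt. Give the smoker share of prompted consultations for each service next to these rates, and average the new rates over services as already planned.

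Build the split into the quarterly extracts for both Pen CS and Communicare before data are aggregated. Table 2 names both systems as sources for change in smoking status, so the field should exist in each. The direct smoking question is described explicitly only for Communicare, so its Pen CS counterpart should be confirmed.

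The cost is a small change to the extract and a smaller denominator per service for B, C and D, hence less precise service-level rates. If it turns out that only smokers are prompted, the two versions coincide and nothing is lost.

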#### Implementation readiness

When engaging the health services, interviews and questionnaires with CEOs, managers, and/or champions will be performed to evaluate the service readiness to implement the intervention. We will evaluate the system, organisational and staff capacity, functional considerations, the culture/climate, senior leadership, implementation plan and training. This baseline evaluation will allow us to identify the stage of the service and assist with the pre‐implementation and preparation. Participants will be invited to an interview and survey. The interview will be conducted over zoom, and the interviewer will share the information of the survey on the screen. The aim of the interview is to collect detailed information about the characteristics of the service before the implementation, and with the survey, we aim to assess the readiness to implement using the “Checklist to Assess Organisational Readiness (CARI) for Evidence Informed Practices Implementation” tool [47].

After concluding with the training, health care providers participating on the research arm will be invited to complete a survey using the NoMAD instrument [48] to assess the implementation process. The aim of this instrument is to include the perspective of individuals involved in the implementation work.

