### Outcome measures for iSISTAQUIT

#### Outcomes related to RE-AIM framework

This study will utilise the RE-AIM framework (Reach, Effectiveness, Adoption, Implementation and Maintenance) to plan, evaluate and report the intervention impact of the implementation of iSISTAQUIT (See Table 2). RE-AIM framework was chosen as it is a widely used implementation model that reports comprehensively on the key issues related to implementation studies- beginning with adoption and reach, followed by implementation and efficacy or effectiveness, and finishing with maintenance [46].

**Table 2 pone.0274139.t002:** RE-AIM framework evaluation.

RE-AIM component	Outcomes	Method of assessment (data sources)	Data sources
Reach	1. Service participation rate	• Number of HS participating in Evaluation-Research package / Number of HS approached (CL, RF) • Number of HS participating in Training only package/ number of HS approached (PTA, CCI)	• PenCS Topbar application or web-based version for iSISTAQUIT (ABCD template) or • Communicare iSISTAQUIT Clinical item (ABCD template)
	2. HCP participation rate	Number of HCP registered to do the training/ number of HCPs determined to be eligible to participate by the service (OM, RF)	
	3. Representativeness	Characteristics of HCPs such as age, sex and region of practice compared with national/regional figures available through national databases and peak bodies data (such as the General Practice Workforce providing Primary Care services in Australia)	Australian Government DOH General Practice Workforce providing Primary care services in Australia (https://hwd.health.gov.au/resources/data/gp-primarycare.html)
Effectiveness	1. Barriers and enablers	A 9 item, 5-point Likert scale (strongly disagree to strongly agree) questionnaire based on the Theoretical Domain Framework [49]. (OS)	• Online (through Moodle) pre-, immediate post- training and 3-month surveys
	2. Knowledge attitudes and practices related to SCC	Knowledge, Attitudes and Practices related to SCC measured through online pre-, immediate post- and 3 months post-training surveys. (OS)	• Online (through Moodle) pre-, immediate post- training and 3-month surveys

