Implementation	1. HCP iSISTAQUIT usage rate	• Number of HCP who used the iSISTAQUIT/ABCD template to engage women in smoking cessation care over the first 3 months /Number of HCP that commenced the training (OM, PTA, CCI) • Analysis of number and type of BCTs used from the template	• Online through Moodle, HPMI at 3 months and 6 months
Maintenance	1. Descriptive statistics (number and percentage)	• HCP’s/services that ask for more iSISTAQUIT resources (treatment manuals, patient flip charts, my journey booklets). (OS, AU) • HCPs that report iSQ training is a current part of their normal work. (OS) • HCPs that report iSQ training will become part of their normal work at 3 months post training. (OS) • Ongoing/long term use of the iSISTAQUIT ABCD template. (PTA, CCI) • Services interested in offering iSISTAQUIT training and resources (if available) to new HCPs joining the service after project completion. (QA)	• Qualitative analysis/audit of qualitative interviews by an external Aboriginal service. • The 3-month HCP survey. • Pen CS Topbar or Communicare de-identified aggregated quarterly data will provide iSISTAQUIT/ABCD template utilisation data until end of current study completion (31 December 2022). • End of study interviews

HS: health services; HCP: health care professional; ABS: Australian Bureau of Statistics.

CPD: Continued professional development; HPMI: Hunter Postgraduate Medical Institute; NRT: Nicotine Replacement therapy; iSQ: iSISTAQUIT

CL: Communication Log

RF: Registration form

RACGP: Royal Australian College of General Practitioners

PTA: Pen CS Topbar application

SCC: Smoking Cessation Care.

CCI: Communicare iSISTAQUIT Clinical Item

OS: Online Survey

QA: Quantitative analysis

AU: Audit

OM: Online through Moodle

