#### Status and timeline

The recruitment of sites has begun and to date 92 health providers have been enrolled and 42 health providers have completed training. Site recruitment will be completed by August 2022. All participating HCPs will complete training by October 2022. Data collection will be completed by November 2022. Data analysis and reporting of results will be completed by December 2022. The social media campaign was launched in December 2021 and evaluation completed by October 2022.

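### Self-reported post-training outcomes have no time point for Option 1 practitioners who start the training but do not finish it

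*Protocol article*

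**What the plan says.** All references are to the protocol article.

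- **Table 2, Effectiveness.** KAP is "measured through online pre-, immediate post- and 3 months post-training surveys". The barriers and enablers questionnaire uses the same three occasions.
- **Implementation readiness.** On NoMAD: "After concluding with the training, health care providers participating on the research arm will be invited to complete a survey using the NoMAD instrument". The stated purpose is to capture the view of the people who do the implementation work.
- **Table 2, Maintenance.** Two online-survey items concern normal work: "HCPs that report iSQ training is a current part of their normal work" and "HCPs that report iSQ training will become part of their normal work at 3 months post training". The second carries its own date. The first does not, but the row lists the 3-month practitioner survey among its sources.
- **Evaluation plan.** KAP is compared from pre-training to the two post-training occasions in a linear mixed model with categorical time and a random intercept for site. No practitioner-level term is named.
- **Table 2, Implementation.** The denominator of the usage rate is "Number of HCP that commenced the training".
- **Table 2, Adoption.** The share of those commencing who complete is itself an outcome.
- **Training delivery.** The course has 14 self-paced modules.
- **Status and timeline.** "to date 92 health providers have been enrolled and 42 health providers have completed training".

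**The concern.** A practitioner who stops partway through a self-paced course has no end-of-training date. The immediate and 3-month surveys and NoMAD therefore have no defined date for that person, although the pre-training survey has been completed. The practitioner may still work at a service that holds the template, the carbon monoxide meter and the oral NRT, and so may be one of the people whose view NoMAD is meant to include.

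People who stop plausibly differ from people who finish in interest, workload or how well the package suits them. An implementation study wants to know about exactly these things. Two results are at stake. The normal-work and NoMAD figures may look better than they would across all who commenced. The pre-post KAP contrast may compare two different groups of practitioners. This is a matter of data collection: an analysis plan can handle missing replies, but it cannot create an invitation afterwards.

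**Working it through.** **1. How far completion can be taken for granted.** From Status and timeline, 42/92 = 45.7% had completed and 50/92 = 54.3% had not. This is an interim count of enrolled practitioners, not split by package, taken while training was open. It is not a dropout rate. The final completion proportion c is unknown, so c = 80% and c = 60% are used below as assumptions.

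**2. The plan's own yardstick.** The Sample size section assumes 20 sites × 8 practitioners = 160, assessed before and after, with 90% power for 0.2 SD at a 5% type 1 error rate. In a paired normal approximation, power = Φ(0.2·√160 / √(2(1−ρ)) − 1.96), where ρ is the pre-post correlation. The article does not state ρ.

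- ρ = 0.5 gives 71.6%.
- ρ = 0.7 gives 90.4%.

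The stated 90% is attainable with ρ of about 0.7 and can be neither confirmed nor faulted from the article. The 160 are described as trained and assessed, so the present point does not change that figure. The 0.2 SD serves here only as a scale for bias.

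**3. Artefact in the KAP contrast.** Let F and N be the pre-training means of finishers and non-finishers, δ = F − N, and suppose nobody changes.

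- Pre-training mean, everyone who answered: cF + (1−c)N.
- Post-training mean, finishers only: F.
- Apparent change: F − cF − (1−c)N = (1−c)δ.

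With δ = 0.2 SD (assumed):

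| Completion c | (1−c) × 0.2 | Share of the 0.2 SD target |
|---|---|---|
| 80% | 0.04 SD | 20% |
| 60% | 0.08 SD | 40% |

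These are upper values. The artefact is smaller if the gap narrows by follow-up, or if part of the gap lies between sites, where the site intercept can absorb it. If non-finishers start higher than finishers, the sign reverses. Restricting both means to the same finishers gives F − F = 0. A practitioner-level random intercept moves the comparison towards within-person differences and removes more of the artefact as the within-person correlation rises.

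**4. Gap between finishers and all who commenced.** If finishers gain 0.2 SD and non-finishers gain nothing (assumed, the unfavourable extreme), the mean gain over all who commenced is 0.2 × 0.80 = 0.16 SD or 0.2 × 0.60 = 0.12 SD. If 80% of finishers report the training as part of normal work and no non-finisher does (assumed), the figure over all who commenced is 0.80 × 0.80 = 64% or 0.80 × 0.60 = 48%.

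**5. Which outcomes are touched.**

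| Outcome | Depends on an end-of-training date? |
|---|---|
| Post-training KAP and barriers surveys | Yes |
| NoMAD | Yes, as worded |
| Normal-work item at 3 months | Yes |
| Usage rate | No: divided by all who commenced; the numerator is template use |
| Women's smoking status and participation | No: taken from practice software and the communication log |
| Ongoing template use, resource requests, service interest | No completion condition stated |
| End-of-study practitioner interviews | No completion condition stated |

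**The case against.** A reader might infer that those who stop are never contacted again. The article does not say so. It is an inference from timing words: nowhere are later surveys said to be locked to completion. The NoMAD invitees are defined as research-arm practitioners, and the end of training could be read as the end of the training phase, which has a planned date of October 2022. Option 1 practitioners consent in advance to four surveys. How surveys reach those who stall may be set out in the full protocol.

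A reader might also infer that Effectiveness, Implementation and Maintenance as a whole describe finishers only. That is not supported. The one rate named under Implementation keeps everyone who commenced, and several Effectiveness and Maintenance outcomes do not depend on a practitioner finishing. Nor is KAP strictly a finishers-only analysis, since non-finishers' pre-training answers enter the model. Non-completion is not hidden either, because Adoption reports it. Measuring change among trained practitioners is a legitimate choice, and the Sample size section speaks of those trained.

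All of this stands and limits the point to the self-reported items. It does not remove it. Adoption shows how many stop, but not what they know, do or think. Interviews cannot supply KAP scores or normal-work percentages. If change among trained practitioners is the intended target, a pre-training mean that includes non-finishers does not match it.

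**Conclusion.** The point holds for the post-training KAP and barriers surveys, NoMAD and the 3-month normal-work item. As worded, an Option 1 practitioner who commences but does not finish has no time point for any of them, so these results will describe mainly finishers. The KAP model as described adds a change in who responds, worth up to about 0.04 to 0.08 SD at 80% to 60% completion if the baseline gap is 0.2 SD. The gap and the completion proportions are assumptions; the article gives neither. The size also rests on the model having no practitioner-level term, which the unseen analysis plan may add. The interim 42 of 92 shows only that completion cannot be assumed. This is an inexpensive improvement to data collection and labelling, and it leaves the other RE-AIM outcomes as they are.

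**What to change.** 1. Send the 3-month KAP and normal-work survey and NoMAD to every Option 1 practitioner who commenced: at 3 months after completion or, if training is not completed, at a fixed interval after commencement. Choose the interval so that it falls before data collection closes.
2. Report the normal-work percentage among respondents and, beside it, over all Option 1 practitioners who commenced. The second figure counts a non-reply as not maintained, so present it as a conservative bound and not as the estimate.
3. If step 1 is not adopted, label the post-training KAP, barriers, NoMAD and normal-work results as completers only.
4. In that case, also restrict the pre-post KAP comparison to the same practitioners, or add a practitioner-level random intercept. The second option uses non-finishers' baseline answers, under an assumption about their later course that the data cannot test.

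The cost is a changed trigger for existing online surveys and a few lines of protocol text. Practitioners log in to the training platform with their own accounts, so linking their surveys should be feasible. Response among non-finishers will probably be low, and the reported figures may be slightly less favourable.
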